## **Packaging, labelling and delivery**

The test preparation is given to the test subjects at home in the form of nasal sprays with a unique identification. The labels on the nasal sprays provide instructions on how often and in what dosage the nasal spray should be taken (see labels in the appendix). The study medication will be provided by KAZ and collected by the study coordinator before the start of the study. Upon receipt of the study medication/study material, an inventory is taken, a Drug Receipt Log is filled out and signed by the person who received the material. A thorough check is made to ensure that the consignment contains all the items on the delivery note. If the delivery contains defective or unusable study medication, this is recorded in the study documents. Regular drug reconciliation regarding allocation, administration and remaining study medication will be performed, documented with the Drug Reconciliation Form, and dated and signed by the study team. At the end of their participation in the study, the subjects return the nasal sprays, which are collected and documented by the study management. The returned nasal sprays will be kept until the end of data collection to enable any cross-checks with regard to blinding.

## **Blinding**

The study is a placebo-controlled double-blind study. This means that the placebo contains all the same ingredients as the original medication - except for the active ingredient. The preparation of the placebo and blinding of the study medication is carried out by KAZ (GMP certificate see appendix). An assistant from the Chair of Clinical Psychology and Psychotherapy (lic. phil. [name]) who is not involved in the study will carry out the randomization using the "Research Randomizer" program and submit the randomization table to KAZ. The KAZ will hand over the table sealed in an envelope to the study management after the preparation of the test sample. This allows the investigator to unblind the code in an emergency. The code should only be broken in an emergency if the identity of the preparation must be known to the investigator in order to ensure the medical care of the participating person. After completion of data collection, the blinding is cancelled.

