### 5.6.3 Ecological Momentary Assessment (EMA)

The measurement of the psychological variables takes place on five days after the first laboratory appointment during four time points, the measurement of the saliva samples on six time points per day. The test subjects are contacted by a signal from the handheld computer (Palm Tungsten E2 handheld, or similar model) and asked to complete the questions on their current state of mind, stress and social interactions directly on the computer. The data is analysed using the freeware program "The Purdue Momentary Assessment Tool" (PMAT). The alarms are triggered at intervals of approximately three hours (Steptoe et al., 2008). In addition, the subjects are asked to perform 6 saliva measurements using salivettes (Salivette®, Sarstedt, Rommelsdorf, Germany) on all five days at the following times: immediately after waking up (measurement 1), 30 minutes after waking up (measurement 2), 2.5 hours after waking up (measurement 3), 8 hours after waking up (measurement 4), 12 hours after waking up (measurement 5) and before going to bed (measurement 6). Measurements 3-6 are compared with the four psychological measurements. The actual time of Salivette ingestion (and thus compliance with the study schedule) will be verified using electronic Aardex MEMS doses (Aardex Ltd, Zug, Switzerland). Drug accountability in sub-study 1 is ensured by asking the subjects at each measurement time point with the handheld computer whether they have taken the 2 sprays per nostril. In addition, the blinding table can be used to trace the batch number dispensed per subject. At the end of the study, the subjects must return the used nasal spray vials to the study coordinator so that the amount of nasal spray liquid actually taken can be verified. Compliance with Syntocinon® is recorded every day using a hand-held computer at and the intake of Syntocinon® is always recorded together with the saliva measurement, which is documented using the Aardex MEMS doses.

During the first laboratory appointment, the test subjects are explained how to use the EMA materials over the next five days. They also receive a written summary containing all the necessary information and telephone numbers for further questions.

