## **Blinding**

The study is a placebo-controlled double-blind study. This means that the placebo contains all the same ingredients as the original medication - except for the active ingredient. The preparation of the placebo and blinding of the study medication is carried out by KAZ. The preparation of the placebo and blinding of the study medication is carried out by KAZ (GMP certificate see appendix). An assistant from the Chair of Clinical Psychology and Psychotherapy (lic. phil. [name]) who is not involved in the study will carry out the randomisation using the "Research Randomizer" program and submit the randomisation table to KAZ. The KAZ will hand over the table sealed in an envelope to the study management after the preparation of the test sample. This allows the investigator to unblind the code in an emergency. The code should only be broken in an emergency if the identity of the preparation must be known to the investigator in order to ensure the medical care of the participating person. After completion of data collection, the blinding is cancelled.

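### The only emergency code-break in each sub-study is the complete randomisation table in one sealed envelope, so unblinding one person reveals every allocation in that sub-study, including future ones

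*Protocol*

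**What the plan says.** Section 5.6.1 (Blinding) has an assistant outside the study generate the randomisation table and send it to KAZ, which prepares and blinds the sprays. Then: "The KAZ will hand over the table sealed in an envelope to the study management after the preparation of the test sample". The purpose follows: "This allows the investigator to unblind the code in an emergency". The limit on its use is that "The code should only be broken in an emergency if the identity of the preparation must be known to the investigator", for the medical care of the participating person. The planned end of blinding is also given: "After completion of data collection, the blinding is cancelled". Section 6.5.2 (Blinding) repeats all of this for sub-study 2. Neither section describes a code for a single couple or participant.

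On timing, section 5.6.1 (Packaging, labelling and delivery) says of sub-study 1: "The study medication will be provided by KAZ and collected by the study coordinator before the start of the study". The storage paragraphs for both sub-studies say that all medication can be ordered and stored in one batch.

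On accountability, section 5.6.3 adds for sub-study 1: "In addition, the blinding table can be used to trace the batch number dispensed per subject". Section 5.6.1 also says: "Regular drug reconciliation regarding allocation, administration and remaining study medication will be performed", documented and signed by the study team.

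**The concern.** The emergency rule concerns one person, but the only tool provided reveals the whole list. It cannot be used as the rule intends without disclosing far more than is needed, and the disclosure cannot be undone.

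Two protections are at stake. The first is allocation concealment. Anyone who has seen the list could know what a couple or person would receive before that couple or person is enrolled. The second is blinding of those who make decisions during the trial. In sub-study 1 the investigator supervises the wounding and the 24-hour fluid sampling (section 5.4.4) and checks the compliance entries at the end of the week. Participants classed as non-compliant are left out of the analysis (section 5.6.1, Compliance). The principal investigator may end a subject's participation on a risk-benefit judgement (section 5.4.3). Decisions about who stays in the trial and who enters the analysis would then be open to influence from known treatment.

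**Working it through.** The protocol gives no figure to reproduce here. The check is a reading of the passages side by side, followed by a count.

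**1. What one opening reveals**

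| Element | Sub-study 1 | Sub-study 2 |
|---|---|---|
| What is in the envelope | the table (5.6.1) | the table (6.5.2) |
| Holder | study management | study management |
| Single-unit code described | none | none |
| Unit for drug allocation | couple; both partners get the same preparation (5.4.4) | person, or person-visit (see step 4) |
| Size | 100 couples (5.4.1) | 88 people (6.4.1) |

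Exposed by one opening as written: up to 100 couples, 100 × 2 = 200 people, in sub-study 1; up to 88 people in sub-study 2. Needed in an emergency: 1 couple (2 people) or 1 person.

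**2. Whether future allocations are included**

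The table is made before the sprays are prepared, and it is handed over once they are. In sub-study 1 the sprays are collected before the study starts, so the list exists before the first couple is enrolled. In sub-study 2 the sprays are fetched in tranches of 10, but the storage paragraph still allows ordering as one batch, and the table goes to KAZ before preparation. Subject numbers are given in ascending order in both sub-studies. On the assumption that the table follows that order, the next allocations can be read from it.

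If the envelope is opened after k couples have enrolled, 100 − k later allocations are known in advance:
- k = 1: 100 − 1 = 99 couples
- k = 50: 100 − 50 = 50 couples

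These values of k are illustrations. The protocol gives no expected rate or time of emergency unblinding.

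**3. Section 5.6.3 against the emergency-only rule**

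Section 5.6.1 allows the code to be broken only in an emergency and ends blinding after data collection. Section 5.6.3 says that "the blinding table can be used to trace the batch number dispensed per subject", and gives no time, no role and no statement that treatment identity is hidden. The protocol describes no other table that links subjects to preparations, so this may be the randomisation table, but that is an inference. The two sections agree if the tracing happens after unblinding or uses a list without treatment identity. They conflict if the sealed table is used during the trial. The text does not settle which is meant.

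**4. Number of individual codes needed**

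- One per couple and one per person: 100 + 88 = 188.
- The sub-study 2 visit plan marks randomisation at both visits, and the 44 women attend twice (6.4.1). If they are randomised at each visit: 44 men × 1 + 44 women × 2 = 132, and 100 + 132 = 232 in all.

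**The case against.** The strongest reply is that this is a matter of handling with a low chance of harm. The subjects are healthy volunteers with short exposure, and section 7.3.1 expects no side effects. An uninvolved assistant makes the list, an external pharmacy blinds the product, the envelope is sealed, and opening is restricted to emergencies. All of this is right and limits the likelihood. It does not change what an opening would disclose, and the protocol itself plans for an opening.

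A reader might infer that the table is a routine accountability tool that will be opened during the trial. The documents do not support that. Section 5.6.3 says only that a blinding table can be used to trace batch numbers. It makes the handheld query the main means of accountability and returned vials the check. Returned sprays are kept until data collection ends for cross-checks on blinding (5.6.1), which fits tracing after unblinding. Sprays already carry a unique identification, and receipt and reconciliation forms exist. What stands is that 5.6.3 and 5.6.1 need to be reconciled, for sub-study 1 only.

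A reader might also infer that wound size would be measured with the allocation known. Section 5.7.2 places the evaluation of wound size, TEWL and epithelialisation in the Dermatology Department and cytokine analysis in a separate laboratory. Nothing says an opened table would reach either. What stands is the exposure of the investigator, who supervises wounding and sampling, and of those deciding on compliance and termination. The compliance exclusion follows a stated rule based on handheld entries, so the room for judgement there is limited.

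The argument is weaker in sub-study 2. Viewing time and gaze are recorded by device, ratings come from the participant, and intake is observed directly. There, the loss is mainly allocation concealment.

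**Conclusion.** The point holds as a defect in the stated method of emergency unblinding. In each sub-study, one opening discloses up to 100 couples (200 people) or 88 people where one couple or one person would suffice, and it includes those still to be enrolled. Concealment of later allocations and the blinding of the investigator and principal investigator would be compromised.

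The conclusion rests on three assumptions: the envelope holds the full table for the sub-study, as the text says; the table can be matched to the ascending subject numbers; and the principal investigator would see what the investigator or study management sees. How often an opening would occur is unknown.

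It should not be read as saying that both sub-studies fall together. The protocol does not say whether they share one table, so full exposure is certain only within a sub-study. Nor does it show that the wound assessors would be unblinded or that the envelope will be opened for accountability. The change is worth making because it is cheap and lost blinding cannot be restored, but the protocol's text does not show that blinding has been or will be broken.

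**What to change.** In sections 5.6.1 and 6.5.2 (Blinding), replace the single envelope with numbered sealed code-breaks issued by KAZ: one per couple in sub-study 1 and one per randomised unit in sub-study 2. State whether women in sub-study 2 are randomised once or at each visit, because that decides whether the code is per participant or per visit. State that KAZ keeps the full table until data collection ends.

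In section 5.6.3, state either that batch tracing during the trial uses the existing spray identification and the dispensing or reconciliation records, without treatment identity, or that the blinding table is consulted only after unblinding. The reconciliation wording in 5.6.1 should say the same about allocation.

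The cost is 188 sealed codes, or 232 if women are randomised at both visits, plus wording changes in three sections. This is a small clerical task for the pharmacy. Sample size, treatment and analysis are unaffected.

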## **Storage conditions**

The study medication is stored refrigerated in the KAZ. The unopened medication has a shelf life of three years. As the medication is not opened for blinding, all medication can be ordered and stored in one batch.

## **Return or destruction of the study medication**

At the end of the study, a final review of the transport, dispensing and whereabouts of the study medication is carried out. This is documented with the Drug Reconciliation Form, dated and signed. Any discrepancies will be investigated, clarified and documented before any remaining study medication is destroyed. The destruction of the study medication is then noted in the study documents.

### 5.6.3 Ecological Momentary Assessment (EMA)

The measurement of the psychological variables takes place on five days after the first laboratory appointment during four time points, the measurement of the saliva samples on six time points per day. The test subjects are contacted by a signal from the handheld computer (Palm Tungsten E2 handheld, or similar model) and asked to complete the questions on their current state of mind, stress and social interactions directly on the computer. The data is analysed using the freeware program "The Purdue Momentary Assessment Tool" (PMAT). The alarms are triggered at intervals of approximately three hours (Steptoe et al., 2008). In addition, the subjects are asked to perform 6 saliva measurements using salivettes (Salivette®, Sarstedt, Rommelsdorf, Germany) on all five days at the following times: immediately after waking up (measurement 1), 30 minutes after waking up (measurement 2), 2.5 hours after waking up (measurement 3), 8 hours after waking up (measurement 4), 12 hours after waking up (measurement 5) and before going to bed (measurement 6). Measurements 3-6 are compared with the four psychological measurements. The actual time of Salivette ingestion (and thus compliance with the study schedule) will be verified using electronic Aardex MEMS doses (Aardex Ltd, Zug, Switzerland). Drug accountability in sub-study 1 is ensured by asking the subjects at each measurement time point with the handheld computer whether they have taken the 2 sprays per nostril. In addition, the blinding table can be used to trace the batch number dispensed per subject. At the end of the study, the subjects must return the used nasal spray vials to the study coordinator so that the amount of nasal spray liquid actually taken can be verified. Compliance with Syntocinon® is recorded every day using a hand-held computer at and the intake of Syntocinon® is always recorded together with the saliva measurement, which is documented using the Aardex MEMS doses.

During the first laboratory appointment, the test subjects are explained how to use the EMA materials over the next five days. They also receive a written summary containing all the necessary information and telephone numbers for further questions.

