## **5.6 Physiological examination methods**

### **5.6.1 Intranasal application of oxytocin**

In a double-blind and placebo-controlled design, participants will take oxytocin (Syntocinon, Novartis, Basel, Switzerland) or placebo intranasally at the first laboratory appointment and then twice daily for 5 days after the first laboratory appointment:

During the 1st laboratory appointment, the subjects take 24 IU (3 sprays in each nostril) before the instruction of the standardized positive interaction/no interaction.

On the day of the first laboratory appointment, the test subjects are asked to spray 2 bursts of oxytocin or placebo into each nostril at 2 times on the following 5 days (together with the saliva vial measurements 4 & 5) (a total of  $2 \times 2 \times 4 \text{ IU} \times 2/\text{day} = 32 \text{ IU}$ ). This procedure is maintained on the following 5 measurement days at home. In total, the test subjects will therefore

ingest 1\*24 and 5 \* 32IU of either oxytocin or placebo (Ditzen, Schaer et al., 2009; [name] et al., 2003; Kosfeld et al., 2005).

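### Section 5.6.3 spaces the four handheld prompts about three hours apart, so they cannot accompany saliva measurements 3 to 6, with which they are to be compared

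*Protocol*

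**What the plan says.** All of the conflicting text is in Protocol section 5.6.3. For the five days at home, the psychological variables are collected "during four time points, the measurement of the saliva samples on six time points per day". The handheld computer signals the participant, and "The alarms are triggered at intervals of approximately three hours". No time is given for the first alarm.

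The six saliva samples are fixed relative to waking: at waking, then 30 minutes, 2.5 h, 8 h and 12 h afterwards, and a last one before bed. The link between the two streams is one sentence: "Measurements 3-6 are compared with the four psychological measurements".

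The EMA paragraph of section 5.4.4 says that saliva and well-being measurements at home are both carried out on a handheld signal. Section 5.6.1 places the two daily spray occasions "together with the saliva vial measurements 4 & 5". Section 5.6.3 checks intake by "asking the subjects at each measurement time point with the handheld computer whether they have taken the 2 sprays per nostril", and later adds that spray use is logged with the saliva sample each time.

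**The concern.** The protocol intends four reports to be set against four samples, one set per occasion. Two of the gaps between those samples are fixed by the protocol at 5.5 h and 4 h, and neither is about three hours. One signal schedule therefore cannot produce both the stated alarm spacing and reports made at the sample times.

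Momentary stress, affect and interaction are recorded next to cortisol and alpha-amylase in order to relate a state to the physiology of the same moment. If the report comes hours before or after the sample, that within-person association is likely to be weakened. If participants instead take saliva at the alarm, the fixed post-waking sampling times are lost. Whichever instruction is followed, the other is broken. Analysis cannot repair this, because a report that was never prompted at the sample time does not exist.

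**Working it through.** **Inputs from section 5.6.3.** Saliva samples 3, 4 and 5 at 2.5, 8 and 12 h after waking; sample 6 at bedtime, *B* hours after waking; four alarms about 3 h apart. **Assumption:** *B* is not given as a clock time, so 14 to 18 h is used as a range. The first-alarm time *a* is not given and is left free.

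**Spans.** Alarms: 3 × 3 = 9 h. Samples 3 to 5: 12 − 2.5 = 9.5 h. Samples 3 to 6: *B* − 2.5 = 11.5 to 15.5 h. To coincide with the samples, the prompts would need gaps of 5.5 h, 4 h and *B* − 12 h (2 to 6 h).

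**Pairing in order.** Alarm *k* falls at *a* plus its step (0, 3, 6 or 9 h). The offset of each pair is (sample time − step) − *a*.

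| Pair | Sample (h) | Step (h) | Sample − step (h) |
|---|---|---|---|
| 1 | 2.5 | 0 | 2.5 |
| 2 | 8 | 3 | 5 |
| 3 | 12 | 6 | 6 |
| 4 | *B* | 9 | *B* − 9 |

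The best *a* is the midpoint of the last column, and the largest offset is then half its range. The first three rows alone give (6 − 2.5)/2 = 1.75 h. The fourth row can only widen the range, so 1.75 h is a floor for every first-alarm time and every bedtime.

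- *B* = 14 or 15: the fourth row is 5 or 6, and the largest offset stays at 1.75 h.
- *B* = 16: (7 − 2.5)/2 = 2.25 h.
- *B* = 18: (9 − 2.5)/2 = 3.25 h.

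If the spacing is stretched to 3.5 h, the first three rows become 2.5, 4.5 and 5, with a floor of (5 − 2.5)/2 = 1.25 h. The largest offset is 1.25 h at *B* = 14, 1.5 h at *B* = 16 and 2.5 h at *B* = 18.

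**Illustration.** With the first alarm at sample 3, the alarms fall at 2.5, 5.5, 8.5 and 11.5 h. The ordered offsets are 0, 2.5, 3.5 and *B* − 11.5 h; the last is 4.5 h at *B* = 16.

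**Matching to the nearest prompt.** With the same alarms, sample 3 coincides with alarm 1, sample 4 is 0.5 h from alarm 3 (8.5 − 8), and sample 5 is 0.5 h from alarm 4 (12 − 11.5). Alarm 2 at 5.5 h is 2.5 h from the closest sample (8 − 5.5). The bedtime sample is *B* − 11.5 = 2.5 to 6.5 h after the last prompt. Three of the four intended pairs can be formed.

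**Intake query.** At 3 h spacing the last alarm precedes sample 5 only if *a* + 9 < 12, that is, if the first alarm is earlier than 3.0 h after waking. With *a* = 2.5 h it does so only for spacing below 9.5/3 = 3.17 h.

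**The case against.** **Nothing stated requires pairing in order.** The protocol says only that the measurements are compared, and electronic monitoring already records the saliva times. Nearest-prompt matching does rescue samples 3 to 5 under a favourable start time, so the large ordered offsets are not inevitable. It does not rescue the comparison as stated, because the bedtime sample is left without a report and one report without a sample.

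**The three hours may be a loose daily average.** Six measurement points from waking to a bedtime at 14 to 18 h average 14/5 = 2.8 to 18/5 = 3.6 h apart. This is possible, but the sentence follows the description of the psychological prompts, and an average says nothing about whether a prompt falls at a sample. Figure 2 is not shown and may give prompt times. It could not make the written interval agree with the written saliva times.

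**The consequences are limited.** This objection stands. A reader might infer that hypothesis I b or the EMA models depend on simultaneous reports and samples. Hypothesis I b in section 5.2 is a randomised contrast of stress parameters between oxytocin and placebo, which needs no paired report. The only EMA model in section 5.7.3 relates EMA data to wound healing.

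**Dose recording.** A reader might also infer that the second daily spray would be recorded as missed, or that participants would be lost under the exclusion rule in the Compliance paragraph of section 5.6.1. The documents do not support this. The problem needs an unstated early first alarm, section 5.6.3 places the intake record with the saliva sample, and returned vials give a further check. How the handheld would code an early answer is not described.

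**Conclusion.** Section 5.6.3 contradicts itself on timing. With exact three-hour spacing and ordered pairing, the worst pair is at least 1.75 h apart for any first alarm and any bedtime. That rises to 2.25 h for an assumed bedtime 16 h after waking and 3.25 h for 18 h. Reading the interval generously as 3.5 h lowers the floor to 1.25 h without removing it. The fixed 5.5 h and 4 h gaps are enough to establish the conflict, so it does not rest on the bedtime assumption.

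What is weakened is the secondary EMA comparison of momentary stress, affect and interaction with cortisol and amylase. The documents give no basis for putting a figure on the loss of association. The randomised contrast in hypothesis I b, the wound-healing outcome and the sample size are unaffected. The order of intake query and spray is a side point to clarify, not a demonstrated fault.

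**What to change.** In section 5.6.3, replace the three-hour interval with prompts anchored to each participant's waking time at the saliva times already stated (2.5 h, 8 h and 12 h), and add a bedtime entry that the participant starts. State that reports and samples are paired by recorded time, using the monitored saliva time and the time of the handheld entry.

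In the same edit, reconcile the handheld intake query with the sentence that ties intake recording to the saliva sample, so that no query comes before the measurement to which it belongs. This concerns only when the question is asked; no change to dose or dose time is proposed.

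The cost is reprogramming the handheld and a short change of text, with no extra samples or prompts. The small downside is that the bedtime report depends on the participant opening it, so some of these entries may be missed.
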